#### 2.8.2. Efficacy evaluation at the time of EOT.

The efficacy evaluation at the time of EOT will result in the following categorizations: effective (in addition to improvements in 1 or more clinical symptoms accompanied by resolution of fever, there will be improvements to pneumonia images or inflammatory findings; WBC < 9000/ mm^3^ or a decrease from the highest CRP level), ineffective, or indeterminable (lack of evaluation information or evaluation items worsening due to causes other than pneumonia).

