#### 2.8.3. Efficacy evaluation at the time of TOC.

TOC will be determined 5 to 10 days after the last dose of the study drug, with subjects classified as being cured, not cured, or indeterminable (lack of evaluation information, evaluation items worsening due to causes other than pneumonia, or clinical symptoms or inflammatory findings improved but the antibacterial drug was prescribed for reasons other than NHCAP before the time of TOC). Cured satisfies all the following criteria: treatment determined to be effective at the time of EOT; or an additional prescription of an antibacterial drug is not necessary after the EOT to the TOC; body temperature, WBC count, CRP level did not deteriorate after EOT, and resulting in an additional prescription of an antibacterial drug not being required; improved symptoms compared to the EOT; and improved chest X-ray compared to the EOT.

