### 2.9. Study endpoints

#### 2.9.1. Primary endpoint.

The primary endpoint is the efficacy evaluation at the time of TOC (5–10 days after the EOT for pneumonia).

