### 2.12. Statistical analysis

The target population in safety analyses (SAS) was defines as patients registered as study participants and administered the study drug at least once during the study period. The target population of the full analysis set (FAS) was defined as a subset of SAS consist of patients who are able to be evaluated whether “cured” or “not cured” at TOC. The modified FAS was defined as an extension of the FAS that includes patients who are able to be evaluated whether “cured” or “not cured” at the TOC or at the withdrawal from the protocol treatment. The target population in the per protocol set analysis was defined as patients with adherence of equal or higher than 80% to the protocol treatment (doses of the study drug).

The objective of the primary analysis is to obtain the lower limit of the 95% CI of the binomial probability of frequency of “cured.” The Clopper–Pearson method was planned to be used here. The FAS was planned as the target population.

A sensitivity analysis for the primary analysis is planned to evaluate the upward bias in the estimation of the probability of the treatment success, that will be introduced by the exclusion of cases who are withdrawn from the protocol treatment before TOC evaluation, obtained from the primary analysis. Aiming this, the modified FAS was set as the target population of the sensitivity analysis and the 95% CI of the binomial probability was planned to be calculated via the Clopper–Pearson method.

The planned analyses on the secondary endpoints are same with the primary analysis; the 95% CI of the binomial probability but the target population, that was set on the FAS.

Associations of the patients background and the primary/ secondary endpoints were planned to be analyzed exploratorily. The patients background was defined as the results from evaluations on respective patients at the visits for the first administration, or before the date, during the patient’s study period.

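### As printed, the primary-endpoint rule for cure demands further improvement after end of treatment, so patients already recovered by then score as not cured; a stray 'or' also leaves effectiveness at end of treatment without force

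*Protocol article*

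**What the plan says.** Section 2.9.1 of the protocol article makes the TOC evaluation the primary endpoint: "The primary endpoint is the efficacy evaluation at the time of TOC". Section 2.12 estimates the probability of cure, with a 95% Clopper–Pearson interval, in patients who can be rated cured or not cured at TOC (the full analysis set, FAS).

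Section 2.8.3 defines cure by a list of which all items must hold. In order:

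- The first two items are joined by an 'or': "effective at the time of EOT; or an additional prescription of an antibacterial drug is not necessary after the EOT to the TOC".
- The third concerns temperature, white cell count and CRP, which "did not deteriorate after EOT, and resulting in an additional prescription of an antibacterial drug not being required".
- The last two are "improved symptoms compared to the EOT; and improved chest X-ray compared to the EOT".

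The same section gives three reasons for rating a patient indeterminable: missing information, worsening from a cause other than pneumonia, and an antibacterial given for another reason before TOC.

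Section 2.8.2 rates a patient effective at EOT on "improvements in 1 or more clinical symptoms accompanied by resolution of fever", plus better images or inflammatory findings. Nothing there prevents a patient from being fully recovered at that visit.

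**The concern.** A patient with no remaining symptoms, or a clear chest X-ray, at EOT has nothing left to improve 5 to 10 days later. Because every item must hold, the rule then fails the patients who responded fastest and most completely. The sentence also applies two standards: temperature and laboratory values need only not get worse, whereas symptoms and X-ray must get better.

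The 'or' raises a second doubt, namely whether effectiveness at EOT is a condition of cure at all.

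The trial has one arm, so a scoring error cannot cancel between groups. It passes straight into the cure rate and its lower confidence limit, which are the main result. Patients are recruited at 24 hospitals, so a rule that can be read in more than one way may also be applied in more than one way.

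**Working it through.** **Notation.** E = effective at EOT. N = no additional antibacterial needed from EOT to TOC. L = the third item (no deterioration, and no additional antibacterial required). S and X = symptoms and chest X-ray improved since EOT. All come from section 2.8.3.

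**Step 1: the rule as printed.** Cured = (E or N) and L and S and X.

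**Step 2: the improvement items.** If S or X is false, the result is not cured, whatever the reason. Resolution by EOT makes S or X false under the wording. It is not among the three reasons for indeterminable, so not cured is the only category left.

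The article's own criteria show that this can happen. Section 2.4 asks for at least one symptom or sign and lists fever among them, so fever alone can qualify. Section 2.8.2 requires fever to have resolved for an effective rating. A patient who entered on fever alone and was rated effective at EOT has no entry symptom left to improve.

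A site that chose indeterminable instead would remove the patient from the FAS, which changes the denominator.

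**Step 3: the 'or'.** L contains the no-additional-antibacterial condition, so L implies N. Whenever L holds, (E or N) is therefore true, and the printed rule reduces to L and S and X. E drops out. Against the all-'and' rule (E and N and L and S and X), and keeping only patterns consistent with L implying N, the two differ in one pattern:

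| E | N | L | S | X | Printed rule | All-'and' rule |
|---|---|---|---|---|---|---|
| 0 | 1 | 1 | 1 | 1 | cured | not cured |

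This patient was not rated effective at EOT, did not deteriorate, needed no further antibacterial, and improved in both symptoms and X-ray afterwards.

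**Step 4: size of the downward effect.** Section 2.11 gives a planning probability of 0.875, a target of 77 patients and an indeterminable share of 0.30. Evaluable patients: 77 × (1 − 0.30) = 53.9, about 54. The article gives no figure for r, the share of true cures already resolved at EOT, so r is an assumption. Expected rate = 0.875 × (1 − r). Count x = 54 × that rate, rounded. Two-sided 95% Clopper–Pearson lower limit = the 0.025 quantile of Beta(x, 54 − x + 1).

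| r (assumed) | Expected rate | x of 54 | Lower limit |
|---|---|---|---|
| 0 | 0.875 | 47 | 0.751 |
| 5% | 0.831 | 45 | 0.707 |
| 10% | 0.788 | 43 | 0.665 |
| 20% | 0.700 | 38 | 0.564 |

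**Step 5: size of the upward effect.** If a share s of the 12.5% true non-cures passed through the pattern in step 3, the rate would be 0.875 + 0.125 × s. At s = 20% this is 0.900 (49 of 54, lower limit 0.797); at s = 40% it is 0.925 (50 of 54, lower limit 0.821). The article gives no figure for s either.

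**The case against.** **The article may not be the operative text.** It describes protocol version 4.0, which is not shown. The odd 'or' and the duplicated clause could be slips of translation or condensation, and investigators may be scoring from clearer instructions. This stands as a limit on the consequence: a reader might infer that sites are in fact scoring recovered patients as failures, and the article does not show that. It does not excuse the printed definition, which is stated rather than omitted.

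**An 'or' can sit inside an 'all' list.** One item with two alternatives is not in itself a contradiction. That is fair. The defect is that the repeated antibacterial clause leaves the EOT item with no effect.

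**The upward effect is easily overstated.** A reader might infer that everyone ineffective at EOT and not re-treated becomes a cure. The text does not allow that: such patients must also show no deterioration and improvement in both symptoms and X-ray after EOT. The subset is probably small, and some of it may be genuine late cures.

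**Comparison with 0.875.** A reader might infer that the trial will fail against that figure. It is only a planning value for the sample size; no test against it is planned, and the cure definition behind it is in a cited report that is not available here.

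**The sizes are assumed.** This is correct: the tables show sensitivity to r and s and estimate neither.

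**Conclusion.** The point holds as a defect in the printed definition of the primary endpoint. Its main part follows from the wording alone: a patient fully resolved at EOT cannot meet the last two items and is scored not cured. By itself this lowers the cure rate in proportion to r, to 0.831 at 5% and 0.788 at 10% if the true rate is 0.875. With about 54 evaluable patients, r = 10% takes the lower limit from 0.751 to 0.665.

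The secondary part is that effectiveness at EOT has no force as printed, which can add cures through one narrow route.

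It is tempting to conclude that the reported rate will be too low overall. The article does not support that, because neither share is given and the two effects oppose each other. What can be said is that the rule is wrong for early complete responders and unclear on the role of the EOT rating.

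**What to change.** Reconcile section 2.8.3 with the full protocol and state cure as one conjunction:

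- effective at EOT;
- and no additional antibacterial for pneumonia from EOT to TOC;
- and temperature, white cell count and CRP not worse than at EOT;
- and symptoms resolved, or improved from baseline and not worse than at EOT;
- and chest X-ray resolved, or improved from baseline and not worse than at EOT.

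Delete the 'or' and the duplicate antibacterial clause. If the 'or' is meant, so that late cures count, say so explicitly.

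Apply the one definition to every enrolled patient. The trial is open-label and section 1 describes it as under way, so record the date of and reason for the change, and report the result under the printed rule as a sensitivity analysis.

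The cost is one paragraph of amendment, matching guidance in the data capture system, and re-scoring of patients already classified. No new assessments should be needed: the printed rule already relies on findings at EOT and TOC, and section 2.4 requires a chest image at entry. Where that image was high-resolution CT alone, the revised text should say how change from baseline is judged.

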#### 2.8.4. Microbiological efficacy evaluation.

The microbiological efficacy is evaluated for each causative bacterium and subject as disappeared, persistent, or indeterminable using the following criteria:

Disappeared, symptoms improved and meet the following:

•Disappeared: Causative bacteria not detected in specimens.•Presumed disappearance: Specimens cannot be obtained.•Colonization: The same causative bacterium is submitted.

Persistent, symptoms do not improve and meet the following:

•Persistent: Causative bacterium is detected in specimens.•Presumed persistence: Culturing of the specimen is difficult or is not performed.•Relapse: The same causative bacterium is detected.•Microbial substitution: The causative bacterium has disappeared but a new causative microorganism is detected (limited to the evaluation of subjects only).•Coinfection: The causative bacterium persists and a new microorganism is detected (limited to the evaluation of subjects only).

Indeterminable, test was not performed.

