#### 2.9.2. Secondary endpoints.

The secondary endpoints are as follows: Clinical efficacy at the time of EOT; Early clinical efficacy 3 days after the first administration; Microbiological efficacy at the time of TOC (each causative bacteria, each subject); Microbiological efficacy at the time of EOT (each causative bacteria, each subject).

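### Microbiological outcome: every assignable listed result follows symptoms, and the categories overlap and leave gaps

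*Protocol article*

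**What the plan says.** Section 2.8.4 states that the outcome is "evaluated for each causative bacterium and subject as disappeared, persistent, or indeterminable using the following criteria". Three results are listed under the heading "Disappeared, symptoms improved and meet the following":

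- "Disappeared: Causative bacteria not detected in specimens"
- "Presumed disappearance: Specimens cannot be obtained"
- "Colonization: The same causative bacterium is submitted"

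The Persistent heading requires that symptoms have not improved. It lists persistence (organism detected), relapse (same organism detected), microbial substitution (original organism gone, new one found), coinfection (original organism still there plus a new one), and "Presumed persistence: Culturing of the specimen is difficult or is not performed". Substitution and coinfection apply to the subject-level evaluation only. The last category reads "Indeterminable, test was not performed" and carries no symptom condition.

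Section 2.9.2 makes this a secondary endpoint at two time points, for example "Microbiological efficacy at the time of TOC (each causative bacteria, each subject"), and likewise at end of treatment. Section 2.12 analyses secondary endpoints as binomial proportions with 95% confidence intervals in the full analysis set.

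**The concern.** A microbiological endpoint should tell the reader what happened to the organism. Here symptoms set the main category, and the specimen result mostly sets only the sub-label. Two consequences follow. First, a reported disappearance rate may include patients whose organism was still found. Second, some patients fit two categories and others fit none, so the numerator and denominator depend on decisions that the article does not fix and that could be made after the data are seen.

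The case for the drug in the Introduction and Discussion is largely bacteriological: breadth of activity and limited resistance. These are the only listed efficacy endpoints that look at bacteria after treatment, so their meaning matters although they are secondary.

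**Working it through.** The article gives no figure for this endpoint, so there is nothing to reproduce. The check cross-tabulates the rules of section 2.8.4 and then illustrates the effect.

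**Step 1. Where each combination falls**

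| Symptoms | Specimen result | Subject level | Bacterium level |
|---|---|---|---|
| Improved | Organism not detected | Disappeared | Disappeared |
| Improved | No specimen obtainable | Disappeared (presumed) | Disappeared (presumed) |
| Improved | Same organism (if detected is meant) | Disappeared (colonization) | Disappeared (colonization) |
| Not improved | Same organism detected | Persistent (persistent or relapse) | Persistent |
| Not improved | Culture not performed | Persistent (presumed) **and** Indeterminable | Persistent (presumed) **and** Indeterminable |
| Not improved | Original gone, new organism found | Persistent (substitution) | **none** |
| Not improved | Original present, new organism found | Persistent (coinfection) | Persistent (organism detected) |
| Not improved | Not detected, no new organism | **none** | **none** |

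The table shows three things.

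- All three results listed under improvement give Disappeared. At subject level, all five listed without improvement give Persistent. No listed result moves a case from one to the other. On the reading in row 3, the same bacteriological finding (rows 3 and 4) is Disappeared or Persistent by symptoms alone.
- Row 5 fits two categories and no order of precedence is given. Row 2 can also overlap with Indeterminable, if no test was done because there was no specimen. That overlap is softer, since being unable to obtain a specimen is not the same as not doing a test.
- The last row has no category at either level. Row 6 has none at bacterium level, because substitution is restricted to subjects.

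**Step 2. Possible effect of the colonization line**

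Assumed, because the article gives no counts: 30 subjects with an evaluable microbiological outcome, 24 Disappeared and 6 Persistent. Of the 24, k improved with the causative organism still detected. Rate without them = (24 − k)/30, with exact Clopper–Pearson 95% intervals.

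| k | Rate | 95% CI |
|---|---|---|
| 0 | 24/30 = 80.0% | 61.4% to 92.3% |
| 3 | 21/30 = 70.0% | 50.6% to 85.3% |
| 6 | 18/30 = 60.0% | 40.6% to 77.3% |
| 9 | 15/30 = 50.0% | 31.3% to 68.7% |

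Each colonization case moves the rate by 1/30 = 3.3 points.

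**Step 3. Possible effect of the overlap**

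Same assumed counts, with 3 of the 6 unimproved subjects untested.

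- Untested counted as Persistent: 24/30 = 80.0% (61.4% to 92.3%).
- Untested counted as Indeterminable and left out of the denominator: 24/(30 − 3) = 24/27 = 88.9% (70.8% to 97.6%).
- Untested counted as Indeterminable but kept in the denominator: 24/30 = 80.0%, unchanged.

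The article does not say how Indeterminable enters the denominator of this endpoint, so the effect lies between 0 and 8.9 points for these counts.

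**The case against.** The strongest counter-argument concerns the colonization line. It does not say that the organism is detected; the verb is unclear and may be a slip. The article condenses a full protocol that is not shown and may be worded properly there. This stands as a limit: reading the verb as detected is an inference from the label and from the parallel relapse line. If the line is a slip, it still needs correcting.

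Allowing for colonization in a patient who has improved is also a classification choice, not an error in itself. That stands too. The objection is to merging such cases into one rate that readers will take as eradication. The sub-labels already allow separation, but the article does not say that the analysis will use them.

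A reader might infer that these endpoints merely repeat the clinical endpoint. The article does not support that. Section 2.8.4 asks only for improved symptoms. Effective at end of treatment (section 2.8.2) also needs fever to resolve and imaging or inflammatory findings to improve, and cured at test of cure (section 2.8.3) adds further conditions. The unit also differs, since results are given per bacterium as well as per subject. The endpoints are related but not identical.

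A reader might also infer a very large overstatement by setting the full Disappeared rate against culture-confirmed cases alone. Much of such a gap could be patients without a specimen, for whom presuming the outcome from symptoms is reasonable. Nor is it true that specimen results never matter: an unimproved patient with no organism found does not fall under Persistent. That patient simply has nowhere to go.

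**Conclusion.** The point holds as a defect in stated rules, not as missing detail. The choice between Disappeared and Persistent follows symptoms in every listed result that can be assigned, and the categories are neither exclusive nor exhaustive. The overlap for untested, unimproved patients and the empty cells follow directly from the text. The overstatement of bacteriological efficacy depends on reading the colonization line as meaning detected.

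The size cannot be derived from the article. Under the assumed 30 subjects, the rate could fall by 10 to 30 points (3 to 9 colonization cases) or rise by up to 8.9 points (3 untested cases excluded). These are illustrations, not estimates.

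The microbiological endpoints at test of cure and end of treatment, and their stratified analyses, are affected. The primary clinical endpoint and the sample size are not. This should be changed, but it does not threaten the trial's main result.

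**What to change.** 1. Correct the colonization line so that it states what specimen result it covers.
2. Assign an unperformed test to one category, with a stated precedence. One option is to use Indeterminable only when neither culture nor clinical outcome is available. State whether Indeterminable cases enter the denominator.
3. At bacterium level, classify an organism that is not detected as disappeared. Keep microbial substitution as Persistent at subject level. A blanket rule that any negative culture means disappeared would override it.
4. Name a subject-level category for unimproved patients with the organism not detected and no new organism found.
5. Report culture-confirmed disappearance with its exact 95% interval, separately from presumed disappearance and from colonization, so that cases with the organism still detected are not counted as eradication.

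The cost is definition wording and derivation code; no new samples are needed. The downside is a lower headline disappearance rate, offset slightly at bacterium level by item 3.

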### 2.9. Study endpoints

#### 2.9.1. Primary endpoint.

The primary endpoint is the efficacy evaluation at the time of TOC (5–10 days after the EOT for pneumonia).

#### 2.9.2. Secondary endpoints.

The secondary endpoints are as follows: Clinical efficacy at the time of EOT; Early clinical efficacy 3 days after the first administration; Microbiological efficacy at the time of TOC (each causative bacteria, each subject); Microbiological efficacy at the time of EOT (each causative bacteria, each subject).

#### 2.9.3. Safety endpoints.

All adverse events that occur during the trial will be recorded.

#### 2.9.4. Exploratory.

The following stratified analyses will be performed for the primary and secondary endpoints: risk of antimicrobial resistance (no or yes),^[2]^ risk of aspiration by (standardized swallowing assessment [SSA]; no or yes),^[13]^ and first to third occupied bacterial species by comprehensive bacterial flora analysis (clone library method).^[14]^

### 2.10. Data collection and management

In this study, data of each patients will be collected by web-based EDC system that electronically prepares case reports. A principal investigator or subinvestigator of the participating medical institutions will input the data needed for the study protocol according to Table 1 to the electric case report in the EDC system. The principal investigator of the participating medical institutions will electronically sign the case reports and ensure that the input data are complete and accurate.

The principal investigator or subinvestigator of the participating medical institutions will confirm that patients meet all the inclusion criteria and do not meet any of the exclusion criteria and input all necessary items into the EDC system. When determined to be eligible, the case registration number issued by the EDC system will be used. The case registration number consists of numbers and symbols unrelated to the information that could identify specific individuals, such as initials and file IDs. When preparing documents related to this study, such as case reports, subjects will be anonymized by the use of case registration number. The principal investigator will prepare a table that shows the patient’s name, number, and so on, so that they can be identified if necessary. This table will be strictly stored and managed so that is cannot be externally leaked. Those involved with this study will make utmost efforts to protect personal information and privacy and are not permitted to share personal information acquired through this study externally without valid reason and permission.

The sponsor-investigator will perform monitoring to review compliance of protocol, each standard operating procedure, and various ministrial ordinances, and reliability of the data. In this study, with the aim of ensuring reliability of this trial, external audit will be conducted. Monitoring and audit will be conducted according to standard operating procedure of monitoring/ audit.

